## Methods and design

### Study design

This study is a randomized, placebo-controlled, double-blind trial investigating bacteriophages in UTI treatment. The study is conducted at the Tzulukidze National Center of Urology (TNCU), Tbilisi, Georgia. Phage preparations (i.e. Pyo bacteriophage solution: commercially available and registered in Georgia) and continuous adaption cycles during the course of the study, to enhance the treatment effect, are done at the Eliava Institute of Bacteriophages, Microbiology, and Virology in Tbilisi (EIBMV), Georgia.

Figure 1 gives an overview of the procedures. Patients planned for transurethral resection of the prostate are screened for UTIs at the TNCU. Urine cultures including antibiotic sensitivity testing are performed in a duplicate manner. If eligible microorganisms which would potentially match with the type of bacteriophage present in Pyo bacteriophage (5 components: Enterococcus spp., *Escherichia coli*, Proteus mirabilis, Pseudomonas aeruginosa, Staphylococcus spp., and Streptococcus spp.) are detected, urine cultures are then sent for bacteriophage sensitivity testing to the EIBMV (Fig. 2) [12]. In case of a positive in-vitro sensitivity testing, concluded within 24 h after receipt of the urine culture, patients will be asked for study participation. After written informed consent, patients are randomized in a double-blind fashion to the study treatment arms in a 1:1:1 ratio to receive either: a) Pyo bacteriophage solution, b) placebo (sterile bacteriology media with identical color as treatment arm a), or c) antibiotic treatment according to the antibiotic sensitivity pattern, respectively. Treatment arms a and b will be double-blind but treatment arm c, i.e. the control arm representing common clinical practice, is open label. All treatments are intended for 7 days starting at the day of surgery (arm c) or one day thereafter (arm a and b). Prior and at the end of treatment (i.e. after 7 days) or at withdrawal / drop out, urinalysis, urine culture, bladder and pain diary [18] and an International Prostate Symptom Score (IPSS) questionnaire [19] will be taken. Patients with persistent bacteriuria will undergo antibiotic treatment according to antibiotic sensitivity.

**Fig. 1 Fig1:**
[figure not shown]
Flow chart of the procedures

**Fig. 2 Fig2:**
[figure not shown]
Bacteriophage sensitivity testing to *Escherichia coli*: The *Escherichia coli* culture reacts positively to 12 phages out of 16. Confluent (complete) lysis can be seen for phages #9, 14 and 16, overgrown (partial) lysis for phages #4, 6, 7, 8, 10, 11, 12, 13, 15 and 16, respectively

Note: As it is common practice when working with bacteriophage cocktails, the Pyo bacteriophage will be subjected to adaptation cycles during the course of the study.

### Study population and recruitment

According to the inclusion and exclusion criteria (Table 1), we will investigate patients planned for transurethral resection of the prostate presenting with UTIs (defined as ≥10^4^ colony forming units/mL and symptoms such as urgency, frequency, and/or dysuria). The following variables will be considered: age, type of bladder emptying, prostate size, urinalysis, bladder and pain diary, IPSS questionnaire.

**Table 1 Tab1:** Study inclusion and exclusion criteria

Inclusion criteria	Exclusion criteria
• Age > 18 years • Urine culture (taken by mid-stream urine; or from the existing transurethral or suprapubic catheter): ≥10^4^ colony forming units/mL of predefined uropathogens (i.e. Enterococcus spp., *Escherichia coli*, Proteus mirabilis, Pseudomonas aeruginosa, Staphylococcus spp., and Streptococcus spp.) • Uropathogens sensitive to Pyo bacteriophage • Symptoms: Urgency, frequency, and/or dysuria • Written informed consent	• Fever >38 °C • CRP >100 mg/L • Acute prostatitis • Concomitant fungal urinary tract infection • Current antibiotic treatment or antibiotic treatment within the last 7 days (exceptions: subjects with an active catheter associated urinary tract infection who have received prior antibiotics may be enrolled provided a minimum of 48 h has elapsed between the last dose of the prior antibiotic and the time of obtaining the baseline urine specimen. Subjects receiving current antibiotic prophylaxis for catheter associated urinary tract infection who present signs and symptoms consistent with an active new catheter associated infection may be enrolled provided all other eligibility criteria are met including obtaining a pre-treatment qualifying baseline urine culture) • Any rapidly progressing disease or immediately life-threatening illness including but not limited to: acute hepatic failure, respiratory failure, and septic shock • No informed consent

### Determination of sample size

We are planning a study of independent cases and controls with 1 control per case. Superiority of bacteriophage versus placebo treatment: We assume the success rate among controls to be 0.2. If the true success rate for experimental subjects is 0.6, we will need to study 27 experimental and 27 control subjects to be able to reject the null hypothesis that the success rates for experimental and control subjects are equal with probability (power) 0.8. The type I error probability associated with this test of this null hypothesis is 0.05.

Non-inferiority of bacteriophage versus antibiotic treatment: We assume the success rate among subjects receiving bacteriophage treatment to be 0.6 and we accept a non-inferiority margin of 0.35. If the true success rate for experimental subjects is 0.95, we will need to study 27 experimental subjects and 27 control subjects to be able to remain within the non-inferiority margin with a probability (power) 0.8. The type I error probability associated with this test of this alternative hypothesis is 0.05. We will use a continuity-corrected chi-squared statistic or Fisher’s exact test to evaluate these hypotheses.

Thus, we will include 27 patients per treatment group, i.e. 81 patients in total. Withdrawn patients will be replaced.

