In line with recommendations of a multi-disciplinary expert panel on acceptance and re-implementation of bacteriophage therapy [11], we therefore designed a randomized, placebo-controlled, double-blind clinical trial to assess the efficacy and safety of intravesical bacteriophage treatment. We hypothesize that intravesical bacteriophage treatment in patients with UTIs due to *E. coli* and other uropathogens, shows a 40% increase in success rate (normalization of urine culture defined as no evidence of bacteria, i.e. <10^4^ colony forming units/mL) as compared to placebo treatment within 7 days. This difference is considered to be clinically relevant. We also hypothesize that bacteriophage treatment is non-inferior to antibiotic treatment in terms of treatment success rates, with a non-inferiority margin of 35%.

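### The non-inferiority sample size assumes a true difference equal to the margin (0.95 − 0.60 = 0.35), so power is about the type I error, not 80%

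*Protocol article*

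**What the plan says.** The Background section of the protocol article gives two efficacy hypotheses. The first is superiority of bacteriophage over placebo. The second is: "We also hypothesize that bacteriophage treatment is non-inferior to antibiotic treatment in terms of treatment success rates, with a non-inferiority margin of 35" per cent.

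The section *Determination of sample size* sizes each comparison separately. For non-inferiority it says:

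- Rate and margin: "We assume the success rate among subjects receiving bacteriophage treatment to be 0.6 and we accept a non-inferiority margin of 0.35".
- Other rate and sample size: "If the true success rate for experimental subjects is 0.95, we will need to study 27 experimental subjects and 27 control subjects".
- Power: these numbers are needed "to be able to remain within the non-inferiority margin with a probability (power) 0.8".
- Type I error: "The type I error probability associated with this test of this alternative hypothesis is 0.05". Whether this is one- or two-sided is not stated.
- Test: "We will use a continuity-corrected chi-squared statistic", or Fisher's exact test, for both the superiority and the non-inferiority hypothesis.

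Allocation is equal, and withdrawals are handled by replacement, not by inflating the sample size.

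**The concern.** A non-inferiority trial is powered at an assumed true difference that lies inside the margin. The further inside it lies, the fewer patients are needed. Here the two stated rates differ by exactly the margin, so nothing is left between the assumed truth and the boundary, and 80% power looked impossible.

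The labels also conflict. Bacteriophage is the experimental treatment and is given 0.6, but the next sentence gives the experimental subjects 0.95.

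At stake is the interpretation of one of the two efficacy hypotheses. If the planning rates are right, the comparison will nearly always fail to show non-inferiority, and a reader who trusts the protocol will take that as the result of a test with 80% power.

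**Working it through.** **Inputs**, all from *Determination of sample size*: bacteriophage rate pT = 0.60; other arm pC = 0.95; margin M = 0.35; n = 27 per arm; power 0.80; type I error 0.05. As sidedness is not given, both one-sided 0.05 and one-sided 0.025 (two-sided 0.05) were tried.

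**Step 1. Where 27 comes from.** The usual formula for a two-sided test of equality, with d = 0.35 and mean rate 0.775, is

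n′ = [z₀.₉₇₅ √(2 × 0.775 × 0.225) + z₀.₈ √(0.60 × 0.40 + 0.95 × 0.05)]² / d²
= (1.157 + 0.451)² / 0.1225 = 21.1

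With the continuity correction:

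n = (n′/4) × [1 + √(1 + 4/(n′d))]² = 26.5, i.e. 27.

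The protocol's figure is reproduced, but as the size needed to show that the arms *differ*. The same formula for the superiority comparison (0.20 v 0.60) gives 27.1.

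**Step 2. The non-inferiority formula with the same inputs.**

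n = (z₁₋α + z₀.₈)² × [pT(1 − pT) + pC(1 − pC)] / [M − (pC − pT)]²

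The denominator is [0.35 − (0.95 − 0.60)]² = 0, so no finite n gives 80%. The normal-approximation power at n = 27 is

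Φ{[M − (pC − pT)]/SE − z₁₋α} = Φ(0 − z₁₋α) = α,

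that is, 2.5% or 5.0%.

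**Step 3. Exact power at 27 per arm**, by enumerating all pairs of binomial counts, with M = 0.35 and bacteriophage 0.60 v antibiotic 0.95:

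| Rule | one-sided 0.025 | one-sided 0.05 |
|---|---|---|
| Wald | 2.9% | 6.2% |
| Newcombe | 3.2% | 6.2% |
| Farrington–Manning | 2.7% | 4.9% |
| Wald, continuity-corrected | 1.8% | 2.9% |

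**Step 4. Other readings of the two rates.**

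- *Labels swapped* (bacteriophage 0.95, antibiotic 0.60): 4 or 5 per arm suffice and power at 27 is close to 100%. This also contradicts the stated bacteriophage rate.
- *Both arms 0.95*: 5 or 7 per arm.
- *Both arms 0.60*: 25 per arm (one-sided 0.05) or 31 (one-sided 0.025) by normal approximation. Exact power at 27 with the first three rules is 84–89% or 76–83%. This reading must discard the stated 0.95.

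**Step 5. What 27 per arm delivers elsewhere** (exact; Wald, Newcombe and Farrington–Manning). The rates are illustrative assumptions, not protocol figures.

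| Bacteriophage v antibiotic | one-sided 0.025 | one-sided 0.05 |
|---|---|---|
| 0.60 v 0.75 | 36–44% | 49–55% |
| 0.82 v 0.95 | 66–71% | 78–80% |
| 0.85 v 0.95 | 79–84% | 88–90% |

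**The case against.** The best defence is that 0.95 was never meant as a belief about antibiotics. It equals 0.60 + 0.35, so it may be the margin boundary typed into software for an equality test, while the real planning assumption was equal rates of 0.60. On that assumption the power at 27 per arm is not far from the stated 0.8, and the fault would be one of description more than of design. This is plausible, and it limits how firmly one can say what the authors believed. It does not save the paragraph, which calls 0.95 a true success rate and nowhere says that the arms are assumed equal. The text needs rewriting on either reading.

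Two smaller points stand. The protocol does not name its sample-size formula, so the match with the equality test is strong evidence of the origin of 27 but not proof. And the superiority formula gives 27.1, which strictly rounds up to 28; the difference is trivial.

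It can also be said that a confidence interval set against the margin would remain interpretable whatever the planned power. That is true, but it does not make the stated power correct.

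**Conclusion.** The paragraph is wrong as written. With bacteriophage at 0.60, the other arm at 0.95 and a margin of 0.35, the assumed truth lies on the non-inferiority boundary. Power is then about 3% (one-sided 0.025) or 5–6% (one-sided 0.05) with the standard rules, and lower with a continuity correction. Non-inferiority would be missed in roughly 94–97% of such trials.

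The size of the error depends on 0.95 being the antibiotic rate, which is the only assignment consistent with the stated bacteriophage rate. The exact percentage depends on the interval method and on sidedness, but every variant is near alpha and far from 80%. The superiority calculation is not affected.

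**What to change.** Rewrite the non-inferiority paragraph so that it:

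- names the bacteriophage and antibiotic arms and gives each one assumed rate;
- states whether alpha is one- or two-sided;
- drops the 80% claim for 0.60 v 0.95;
- reports the power the design has, and the interval method used to compute it.

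Possible wording, assuming one-sided 0.025: *With 27 patients per arm and a margin of 0.35, power is about 76–83% if both true success rates are 0.60 and about 80% if they are 0.85 (bacteriophage) and 0.95 (antibiotic), depending on the interval method. If they are 0.60 and 0.95 it equals the type I error.* If one-sided 0.05 is intended, the first two figures become 84–89% and 88–90%. The sponsor should choose the scenario it believes and justify it.

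Keep 27 per arm. Whether non-inferiority stays alongside superiority or becomes secondary is the sponsor's choice; the correction does not require it.

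The cost is protocol wording and a less favourable power statement. No patients, visits or measurements are added.

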#### Univariate analysis

T-tests will be used to compare means between groups and chi-squared tests to compare dichotomous variables.

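### Non-inferiority to antibiotic is to be judged with tests of equal success rates, which never use the 0.35 margin

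*Protocol article*

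**What the plan says.** The Background section gives the second hypothesis: "We also hypothesize that bacteriophage treatment is non-inferior to antibiotic treatment in terms of treatment success rates", with a margin of 35%. Determination of sample size repeats that "we accept a non-inferiority margin of 0.35". It describes the superiority comparison in one paragraph and the non-inferiority comparison in the next, and ends the second with the only test named for either: "We will use a continuity-corrected chi-squared statistic or Fisher’s exact test to evaluate these hypotheses". The plural, placed there, covers both hypotheses.

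The Data analysis section adds nothing specific to non-inferiority. Univariate analysis provides for "chi-squared tests to compare dichotomous variables", and Multivariate analysis for logistic regression to adjust for baseline imbalance. The article gives no null hypothesis shifted to -0.35, no confidence limit to be compared with -0.35 and no rule for declaring non-inferiority. The margin appears only in the hypothesis and in the sample-size text.

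**The concern.** Non-inferiority needs the null hypothesis that bacteriophage success minus antibiotic success is -0.35 or lower, and evidence that rejects it. The continuity-corrected chi-squared and Fisher's exact tests, as named, have the null that the two rates are equal. A non-significant result from them does not show that the deficit is below 0.35, and a significant deficit does not show that it exceeds 0.35.

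If lack of significance is taken as non-inferiority, the incentive is reversed: the smaller the trial, the easier the claim. With 27 v 27 patients, large deficits often go undetected. What is at stake is one of the trial's two hypotheses on its primary outcome, that bacteriophage can stand in for antibiotic.

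**Working it through.** **Inputs** (Determination of sample size): 27 per arm; margin 0.35; bacteriophage rate 0.60; the other rate 0.95; type I error 0.05, sidedness not stated; power 0.80; placebo rate 0.20.

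**1. Which test produced the 27?** The sample size for a two-sided test of equal rates is

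n0 = [z(0.975)·√(2·p̄(1−p̄)) + z(0.80)·√(p1(1−p1) + p2(1−p2))]² / d²

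and with continuity correction n = (n0/4)·[1 + √(1 + 4/(n0·d))]².

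- 0.60 v 0.95 (d = 0.35, p̄ = 0.775): n0 = (1.1575 + 0.4513)² / 0.1225 = 21.13, and n = 26.5, so **27**, the protocol's figure.
- 0.20 v 0.60 (d = 0.40, p̄ = 0.40): n0 = (1.3579 + 0.5323)² / 0.16 = 22.33, and n = 27.1, so 27 to the nearest integer or 28 rounded up. The protocol states 27.

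The non-inferiority sample size is therefore reproduced by a test of equal rates. A margin-based formula with bacteriophage 0.60 and antibiotic 0.95 leaves margin minus difference = 0.35 − 0.35 = 0, so no finite n exists.

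**2. How often is the named test non-significant when bacteriophage is worse by exactly 0.35?** All 28 × 28 possible tables were enumerated with binomial probabilities. The non-significant column is P(two-sided Fisher p ≥ 0.05). The other two are the probability that the lower 95% limit for bacteriophage minus antibiotic lies above −0.35.

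| Bacteriophage v antibiotic | Fisher non-significant | Newcombe limit | Miettinen-Nurminen limit |
|---|---|---|---|
| 0.60 v 0.95 | 16.0% | 3.2% | 2.7% |
| 0.50 v 0.85 | 27.3% | 3.4% | 2.9% |
| 0.30 v 0.65 | 37.4% | 4.4% | 2.4% |

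Each row is a false claim of non-inferiority. Only the first pair of rates is the protocol's own; the other two are assumptions that show the range. At 0.60 v 0.95, Fisher is significant in 84.0% of trials, which is evidence that bacteriophage is worse.

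**3. A deficit inside the margin.** At true rates of 0.60 v 0.80, Fisher is non-significant in 73.7% of trials, while the Newcombe 95% limit excludes −0.35 in only 28.7%.

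**4. One data set.** 16/27 v 22/27: difference −6/27 = −0.222; Fisher p = 0.135, corrected chi-squared p = 0.136. The Wilson limits are 0.407 to 0.755 and 0.633 to 0.918. The Newcombe lower limit is −0.222 − √[(0.593 − 0.407)² + (0.918 − 0.815)²] = −0.434, and the upper limit is +0.021. The result is not significant, yet non-inferiority is not shown. By contrast, 16/27 v 16/27 has a lower limit of −0.246 and does meet the margin. Fisher labels both results non-significant.

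**5. Direction of the disagreement.** Many tables at 27 v 27 are non-significant on both named tests but fail the margin on the Newcombe 95% limit. None is significantly worse on both tests while meeting it. The substitution therefore errs only towards claiming non-inferiority.

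**The case against.** - **The article nowhere says that non-significance means non-inferiority.** This is true, so the percentages in steps 2 and 3 are conditional on that reading. But with only these tests and no margin-based rule, it is the one route they leave to the claim short of bacteriophage beating antibiotic.
- **Chi-squared statistics with a null shifted to the margin exist and may have been meant.** The sample-size text ties equal rates explicitly to the superiority paragraph only, and speaks of staying within the margin in the other. However, no shifted version is named, Fisher's exact test as named is a test of equality, and the 27 comes from an equality calculation.
- **A significant result in favour of bacteriophage would also establish non-inferiority.** This stands. The named tests fail for every other outcome.
- **A condensed article may leave the decision rule to the full protocol or SAP.** Silence would be excused on that ground. Here the article names a test for this hypothesis, and an SAP that follows it inherits the error.
- **The highest figure uses rates the protocol does not assume, and one-sided 0.025 is a choice.** Both stand. At the protocol's own rates the figure is 16%, still more than three times 0.05. One-sided 0.025 corresponds to the two-sided 0.05 that reproduces the 27.

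**Conclusion.** The plan is wrong as written on this point. The tests fixed for the non-inferiority hypothesis address a different null and ignore the margin. If non-significance is read as non-inferiority with 27 v 27 patients, the false-claim probability at a true deficit of 0.35 is 16% at the protocol's rates and reaches 37% over the rates examined. A margin-based Miettinen-Nurminen rule holds it to 2.4–2.9% at the same points. These figures assume 27 evaluable patients per arm, independent binomial outcomes and a two-sided 0.05 level for the named test. That the tests do not use the margin depends on none of these assumptions.

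**What to change.** Replace the sentence on tests with two:

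- Superiority over placebo is tested with the continuity-corrected chi-squared or Fisher's exact test; choose one in advance.
- Non-inferiority to antibiotic is concluded if the lower limit of the two-sided 95% Miettinen-Nurminen score interval for bacteriophage minus antibiotic success lies above −0.35, at one-sided 0.025.

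A Farrington-Manning test at one-sided 0.025 is nearly the same rule; the two differ only by a small-sample variance factor, here 54/53. If another one-sided level is preferred, state it.

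The analysis change costs one sentence in the protocol and SAP and uses standard software. The non-inferiority power statement must also be restated. With 0.60 v 0.95 the true difference sits on the margin, so a correct rule succeeds in only about 3% of trials. The text also attaches the higher rate to the wrong group: "We assume the success rate among subjects receiving bacteriophage treatment to be 0.6", but then "If the true success rate for experimental subjects is 0.95". An assumed true deficit smaller than 0.35 is needed.

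As an illustration, assume both rates are 0.60. Then n = (1.960 + 0.842)² × (0.24 + 0.24) / 0.35² = 30.8, so 31 per arm at one-sided 0.025, or 25 at one-sided 0.05. Keeping 27 per arm gives 77% power with the Miettinen-Nurminen rule at one-sided 0.025. The cost in patients under that assumption is therefore nil if 77% is accepted, or four more per arm.

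### The superiority test is left as corrected chi-squared or Fisher with no rule for choosing; naming one test, preferably Boschloo's, closes the choice and adds about 5 points of power at 27 v 27 for a wording change

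*Protocol article*

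**What the plan says.** The section of the protocol article on determination of sample size plans the superiority comparison as follows:

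- Placebo rate: "We assume the success rate among controls to be 0.2".
- Bacteriophage rate and number: "If the true success rate for experimental subjects is 0.6, we will need to study 27 experimental and 27 control subjects".
- Error rate: "The type I error probability associated with this test of this null hypothesis is 0.05". The number of sides is not stated.
- Power: 0.8.

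After setting out both hypotheses, superiority and non-inferiority, the same section says "We will use a continuity-corrected chi-squared statistic or" Fisher's exact test to evaluate them. Nothing says which of the two applies, or when. Withdrawn patients are to be replaced, so 27 v 27 is the intended final count.

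The section on univariate analysis has one sentence on tests: "T-tests will be used to compare means between groups and chi-squared tests to compare dichotomous variables". It mentions neither a correction nor Fisher's test. It does not name the primary endpoint, which is dichotomous (normalised urine culture after 7 days).

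**The concern.** The primary superiority result rests on one 2 x 2 table of about 54 patients. At that size the choice of test can decide whether p falls below 0.05. The article gives two alternatives in one place and a general phrase in another, so its text does not fix which p-value is the primary one.

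The second issue is efficiency. In small arms, Fisher's test and the corrected chi-squared have a true type I error well below the nominal 0.05. An exact unconditional test can use more of the allowed error, stay within it, and turn the difference into power without extra patients. Planned power has almost no reserve, so this is worth having.

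**Working it through.** **Inputs.** From the sample-size section: success rates 0.6 and 0.2, type I error 0.05, power 0.8, 27 per arm, 1:1. Two-sided testing is an assumption, because only a two-sided corrected calculation comes close to 27.

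**1. Reproduce 27 per arm.** With mean rate 0.4 and difference 0.4, the uncorrected formula is

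m = [1.960 x sqrt(2 x 0.4 x 0.6) + 0.842 x sqrt(0.6 x 0.4 + 0.2 x 0.8)]^2 / 0.4^2 = (1.358 + 0.532)^2 / 0.16 = 22.3, or 23 per arm.

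With the continuity correction,

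n = (m/4) x [1 + sqrt(1 + 4/(m x 0.4))]^2 = 5.58 x (1 + 1.203)^2 = 27.1.

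That is 28 if rounded up and 27 if rounded to the nearest whole number. One-sided versions give 18 (uncorrected) and 23 (corrected). Exact enumeration agrees with the plan: Fisher and the corrected chi-squared have power 0.799 at 26 per arm and 0.802 at 27.

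**2. Compare the tests at 27 v 27.** All 28 x 28 = 784 possible tables were enumerated. Power is the sum of Bin(x; 27, 0.6) x Bin(y; 27, 0.2) over the tables that a test rejects. Size is the same sum with one common rate in both arms, maximised over that rate. Boschloo's test takes the two-sided Fisher p-value as its statistic and finds its cut-off by the same maximisation. Here it rejects when Fisher p is at most 0.0772.

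| Test, nominal 0.05 | Power, 0.60 v 0.20 | Maximum size | Size at common rate 0.20 |
|---|---|---|---|
| Fisher | 0.802 | 0.026 | 0.019 |
| Corrected chi-squared | 0.802 | 0.026 | 0.019 |
| Uncorrected chi-squared | 0.868 | 0.057 | 0.057 |
| Boschloo | 0.855 | 0.045 | 0.041 |

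Fisher and the corrected test differ in 0 tables. Fisher and the uncorrected test differ in 52. For example, 12/27 v 5/27 gives p = 0.077 (Fisher), 0.079 (corrected) and 0.040 (uncorrected). Boschloo's gain is 0.855 - 0.802 = 0.053 from the rounded figures (5.2 points unrounded). If the assumptions slip, power rises from 0.649 to 0.729 at 0.60 v 0.25, and from 0.550 to 0.627 at 0.50 v 0.20.

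**3. Repeat with unequal arms (bacteriophage v placebo).** At 27 v 26:

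| Test | Power, 0.60 v 0.20 | Maximum size |
|---|---|---|
| Fisher | 0.823 | 0.036 |
| Corrected chi-squared | 0.791 | 0.027 |
| Boschloo | 0.852 | 0.045 |

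Fisher and the corrected test now disagree in 14 tables. For example, 13/27 v 5/26 gives p = 0.042 (Fisher) and 0.053 (corrected). At 27 v 25 they disagree in 24 tables. At 27 v 26 Boschloo gains 0.852 - 0.823 = 0.029 over Fisher and 0.852 - 0.791 = 0.061 over the corrected test.

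**The case against.** The strongest reply is that nothing here is an error. Fisher and the corrected chi-squared are standard and control the type I error, and 27 per arm was chosen for conservative tests and delivers the 80% promised. That stands: the power argument is about efficiency and repairs nothing.

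A reader might infer that the article names three conflicting tests for the primary endpoint, one of which breaches 0.05. The text does not support this. The sentence in the univariate section is general, does not say that the test is uncorrected, and need not override the specific sentence in the sample-size section. A corrected chi-squared is still a chi-squared test. The size of 0.057 arises only if the general sentence is read as an uncorrected test that governs the primary comparison.

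A reader might also infer that half of the 0.05 is always left unused and that 5 points are always gained. Both figures belong to 27 v 27. At 27 v 26 Fisher's maximum size is 0.036 and the gain over Fisher is about 3 points; with 25 on bacteriophage and 27 on placebo it is only about 1 point (0.828 to 0.839).

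Finally, an analysis plan that is not shown may settle the test, so the article does not establish that the choice stays open once data are seen. What remains is that the article itself addresses the test and leaves two alternatives.

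**Conclusion.** The point holds as a modest, low-cost improvement. The planned number of patients and the stated power are sound for the tests named. Two things remain. The open choice is harmless at exactly 27 v 27 but can change the verdict once the arms differ by a single patient. And a valid exact test that rejects whenever Fisher does gains about 5 points of power at 27 v 27, and at 27 v 26 about 3 points over Fisher or 6 over the corrected test, with maximum size still below 0.05.

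These results assume two-sided testing at 0.05, independent binomial arms and the planned rates of 0.60 and 0.20. Replacement of withdrawn patients makes equal arms likely but does not guarantee them. The results cover superiority only.

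**What to change.** Before unblinding:

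- Name one primary test for bacteriophage against placebo: the two-sided Boschloo exact unconditional test at 0.05. State the two-sided convention (here, the two-sided Fisher p-value as the statistic).
- Report the risk difference with a 95% confidence interval, for example Miettinen-Nurminen, and say that the test decides if the two disagree at the border.
- Make the univariate section refer to this test for the primary endpoint.
- Keep Fisher's exact test as a sensitivity analysis.

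If the sponsor prefers Fisher or the corrected test, naming just one of them still closes the open choice, without the power gain. The non-inferiority comparison shares the same sentence and should be specified separately.

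The cost is wording only: no added patients, no change in conduct, and the test is available in standard software.
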